### Data collection

Subject demographics will be collected during the recruitment process. Data on primary and secondary outcomes will be collected by professional outcome assessors at baseline, at 4 weeks of intervention, and at 6 weeks of intervention. All outcome assessors had standardized training on test methods prior to intervention to ensure that all subjects had the same test conditions. To ensure the attendance of students and provide more complete data results, we will provide all students with free professional TT teaching services, free knee pain treatment, and a reward of 100 yuan. It will be released via WeChat after 6 weeks of intervention.

### Data management

The primary and secondary results of the test will be recorded through the case report form (p-CRF), and the paper version of the data will be processed electronically through the free data management software EpiData Manager on time. Two result evaluators separately reviewed and confirmed the data, and converted it into a format that can be used for statistical analysis.

### Statistical analysis

Statistical analysis will be performed by the Statistical Package for Social Sciences (The Statistical Package for Social Sciences, SPSS 23, SPSS Inc., Chicago, IL, USA). ShaPiro Wilk will be used to test whether the variables of the two-way multivariate analysis of variance conform to the normal distribution. One-way multivariate analysis of variance will be used to compare the baseline age, height, and weight data of participants, to explore whether there is homogeneity between groups. Descriptive statistical analysis will be conducted in the form of mean ± standard deviation. Two-way multivariate analysis of variance will be used to perform inference analysis on the effect of the intervention group (e.g., TT + KT, KTp + TT, KT, CON) and time (e.g., pre-intervention, during intervention, post-intervention), in order to examine group effect and time effect and The interaction effect of time and group. Pairwise comparisons of variables with significant effects in ANOVA will be conducted by post hoc analysis and Bonferroni correction to find time effects by group and group effects by time. According to Cohen’s method, the effect size will be divided into large (0.8), medium (0.50–0.79), and small (0.20–0.49) to judge the significance of the intervention effect [55]. *P* < 0.05 means there is a significant difference, and *P* < 0.01 means the difference is extremely significant.

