Currently, there is insufficient evidence to demonstrate the effect of TT or combined with KT on the efficacy and postural control of patients with PFPS. At the same time, the longer the duration of patellofemoral pain, the less successful the treatment will be [32]. Therefore, this paper takes PFPS patients as the intervention object and observes the effect on the curative effect and posture control of PFPS patients through TT or combined KT intervention. Evidence support for prevention.

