### Study design

This is a single-blind randomized controlled trial that recruited 72 eligible early PFPS patients and randomly divided them into 4 groups: TT + KT group, TT + KTp group, KT group, and CON group with a ratio of 1:1. The TT + KT group was intervened with TT combined with intramuscular tape; the TT + KTp group was intervened with TT and intramuscular tape with placebo technical intervention; the KT group was intervened with intramuscular tape alone; the CON group was performed with routine activities. Measurements will be taken at baseline, mid-intervention (4 weeks), and post-intervention (6 weeks) to examine the maintenance of any intervention effects.

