### Sample size calculation

The sample size was estimated by the software G*Power 3.1.9 [33]. According to the experimental design of 4 (group) * 3 (time) in this study, repeated measures analysis of variance was used to test the research hypothesis. Under the effect size of 0.25, α of 0.05, and power of 0.8, the sample size requirement was 64 people. After considering the dropout rate of 10%, the overall sample size was calculated to be 71 people. At the same time, combined with the proportionality of the sample size between groups, the final sample size was determined to be 72 people, and each group was about 18 people.

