### Participant eligibility

PFPS patients were recruited for sports-specialized college students at a university in Beijing. Diagnostic criteria [34–36] are as follows: (1) retropatellar or peripatellar pain for ≥ 4 weeks; (2) at least two induced pains when completing functional activities such as hopping on one foot, going up and down stairs, squatting, running, kneeling, and bending knees for a long time; (3) VAS score ≥ 2 when the pain was the most severe in the last week; (4) Lysholm score < 70; (5) at least two of the following signs were positive: tenderness on the patella or patella circumference, crepitus on the patellofemoral joint surface, Fear test, patellofemoral grinding test, knee extension resistance test, single foot squat test. Inclusion criteria were (1) aged 18–30 years; (2) met the diagnostic criteria and had unilateral involvement; (3) did not receive medication or physical therapy; (4) voluntarily signed informed consent. The exclusion criteria were: (1) damage to the tissues around the knee; (2) structural damage to the knee, such as fracture, meniscus tear, or osteoarthritis; (3) allergy to KT; (4) physical activity Medical contraindications (such as cardiovascular disease); and (5) Inability to adhere to the intervention due to personal or other reasons. All subjects voluntarily signed a written informed consent form before the intervention and were given an explanation of the research process by the researchers, strictly following the ethical standards of the Declaration of Helsinki.

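### Pain duration, the one factor the protocol links to treatment success, is in neither the baseline comparison nor the outcome model; any association of duration with change stays in the residual

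*Protocol article*

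**What the plan says.** The Background gives, as part of the case for the trial, the statement that "the longer the duration of patellofemoral pain, the less successful the treatment will be". It is the only variable the article links to how well treatment works; the other factors listed there are proposed causes of the condition.

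Participant eligibility requires "retropatellar or peripatellar pain for ≥ 4 weeks" and states no upper limit. Study design describes random allocation to four arms ("KT group, and CON group with a ratio of 1:1"), and no stratification factor is named there or under Randomization, allocation, and blinding.

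Statistical analysis then fixes two things. The first is a baseline comparison: "One-way multivariate analysis of variance will be used to compare the baseline age, height, and weight data of participants", with the purpose "to explore whether there is homogeneity between groups". The second is a two-way model of group and time, fitted "in order to examine group effect and time effect and The interaction effect of time and group". Duration is in neither, and no covariate is named.

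**The concern.** The section names the baseline variables, the test, its purpose and the model terms. This is therefore a stated choice, and it does not fit the protocol's own premise about duration.

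The baseline test does not do its job. Under proper randomisation, any baseline difference arises by chance, so the P value tests a hypothesis already known to be true. It says little about whether an imbalance is large enough to matter. It also covers three variables that the protocol never calls prognostic, so a reassuring result on them carries no direct information on duration.

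The outcome model leaves in the residual any part of the change over six weeks that goes with duration. With small arms this has two consequences: standard errors are larger than they need to be, and the single realised estimate can be moved by an imbalance that the planned report would not show.

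**Working it through.** **Inputs.** From the article: 72 patients in 4 arms, so 72/4 = 18 per arm, and three time points including pre-intervention ("According to the experimental design of 4 (group) * 3 (time) in this study"). The article gives no figure for the association of duration with outcome. Assumed: r, the correlation of (log) duration with change, from 0 to 0.5.

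**The plan's own figure.** The required total of 64 can be reproduced from effect size 0.25, alpha 0.05 and power 0.8, for example with the interaction test at a within-patient correlation of 0.2, an input the article does not state. Then 64 × 1.10 = 70.4, rounded up to 71, and 72 for equal arms. The point here does not depend on this total.

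**1. Chance imbalance in duration**
- SD of the difference between two arm means, in SD units of duration: √(2/18) = 0.333.
- A given pair differs by at least 0.5 SD: z = 0.5/0.333 = 1.5, two-sided probability 0.134.
- At least one of the 6 pairs does: studentized range with 4 means, q = 0.5 × √18 = 2.12, probability 0.44. The median largest gap is 0.47 SD.
- With 16 per arm after dropout, the two probabilities are 0.157 and 0.49.

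**2. Would testing duration as well help?** Power of a four-arm F test at 0.05 with one arm shifted by 0.5 SD: noncentrality 18 × 0.5² × (3/4) = 3.375 on 3 and 68 degrees of freedom, power 0.29. Adding duration to a significance test would not settle the matter. This figure is for a one-variable test, not for the planned three-variable one.

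**3. Which effect of duration survives the planned model?** The pre-intervention value is a level of time. If duration shifts a patient's score by the same amount at every visit, that shift drops out of all within-patient contrasts and so out of group by time. With complete data, a duration main effect alone therefore leaves the interaction estimates and their standard errors unchanged. Only an association with change matters for this term, and only a duration by time term removes it.

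**4. Size of the effect on change**

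| r (assumed) | Shift from a 0.5 SD imbalance (0.5r) | SD of chance shift, given pair (0.333r) | Residual variance removed (r²) |
|---|---|---|---|
| 0 | 0 | 0 | 0% |
| 0.2 | 0.10 SD | 0.07 SD | 4% |
| 0.3 | 0.15 SD | 0.10 SD | 9% |
| 0.5 | 0.25 SD | 0.17 SD | 25% |

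Shifts are in SDs of change.

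**5. Cost if duration is not prognostic.** With 72 − 4 = 68 error degrees of freedom, one covariate inflates the variance of a contrast by about 1 + 1/(68 − 2) = 1.015, or 1.5%. Adjustment breaks even at r² = 1/67, r ≈ 0.12.

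**6. Effect on power.** Take one contrast with unadjusted power of about 0.55. Simulation with the adjusted analysis gives about 0.55 at r = 0, 0.57 at r = 0.3 and 0.67 at r = 0.5. A normal approximation agrees. Power 0.55 corresponds to a standardised effect of 1.96 + 0.13 = 2.09. At r = 0.5 the variance factor is 0.75 × 1.015 = 0.761, and 2.09/√0.761 = 2.40, power 0.67. At r = 0.3 it is 0.91 × 1.015 = 0.924, and 2.09/√0.924 = 2.17, power 0.58.

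**The case against.** The other side has a good case against any stronger reading.

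- **Bias.** A reader might infer that an uncorrected imbalance invalidates the comparison. It does not: under randomisation it neither biases the test on average nor inflates the type I error. This stands.
- **Baseline severity.** If long-standing pain simply means worse scores throughout, group by time already removes it. This stands, and it limits the point to an association with change.
- **Strength of the premise.** A reader might infer that the protocol treats duration as decisive. The Background gives one cited sentence with a direction and no effect size. It could also mean that duration modifies the treatment effect, which a covariate common to all arms would not capture. The trial enrols early disease, which may narrow the range of duration, although eligibility sets no ceiling. An r near zero is not excluded.
- **Likelihood.** The 0.44 is for any of six pairs. For one named contrast it is 0.13.
- **Data already held.** Eligibility needs only a yes or no at 4 weeks, so duration in weeks cannot be assumed to be on file.
- **Use of the baseline test.** The article calls it exploratory and ties no analysis decision to it. That a non-significant result would be taken as proof of comparability is conjecture.
- **Scope.** Covariates are often left to an analysis plan. This stands only in part: the article itself names the baseline test and the model terms, so a later plan that added duration would be changing a stated choice.

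**Conclusion.** The point holds in a limited form. The protocol names one predictor of treatment success, then judges comparability on three other variables and fits a model that cannot use the predictor. What is lost is precision, together with some protection against a misleading estimate in this one trial; the validity of the test is not at stake.

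The imbalance probabilities (0.13 for a given pair, 0.44 for any of six) rest only on 18 per arm and approximate normality of log duration. The benefit rests on r, which the documents do not give: nothing at r = 0, small at 0.2 to 0.3, worthwhile at 0.5. It would be tempting to quote the upper end as a saving in patients, but nothing in the article supports a particular r. The case for the change is that the possible gain is real and the loss, if duration proves irrelevant, is about 1.5% in variance.

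**What to change.** In Statistical analysis:

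1. Delete the baseline MANOVA. Replace it with a descriptive table by arm, without P values, that includes symptom duration and the baseline score of each outcome alongside age, height and weight.
2. Pre-specify log duration together with its interaction with time as covariates in the model for every outcome. A main effect alone is not enough, because it leaves group by time unchanged when data are complete. An equivalent route is a model of the 4- and 6-week outcomes with log duration and the baseline score as covariates.

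In Data collection: record duration of pain in weeks at screening, before allocation.

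The choice should be fixed before outcome data are seen. The cost is one extra number on the case report form, revised wording, and a few degrees of freedom per outcome (1 for log duration and 2 for its interaction with three time points). No additional patients are needed.

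### The sample size section tests the hypothesis with a repeated-measures ANOVA, but the analysis section names a two-way MANOVA of group and time without saying that time is within-patient; run literally, it gives wrong error rates

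*Protocol article*

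**What the plan says.** The Sample size calculation section of the protocol article describes a design of four groups by three times and states that "repeated measures analysis of variance was used to test the research hypothesis". On that basis, "Under the effect size of 0.25, α of 0.05, and power of 0.8, the sample size requirement was 64 people", raised for dropout to 71 and set at 72: "the final sample size was determined to be 72 people, and each group was about 18 people".

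The Statistical analysis section names another method: "Two-way multivariate analysis of variance will be used to perform inference analysis on the effect of the intervention group" and time, to examine the group effect, the time effect and their interaction. It gives time three levels (before, during and after the intervention). It does not call time repeated or within-subject. Variables that show significant effects, there described as effects in an ANOVA, go on to Bonferroni-corrected pairwise comparisons, by group and by time.

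The Data collection section confirms that outcomes are taken on each participant "at baseline, at 4 weeks of intervention, and at 6 weeks of intervention".

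**The concern.** Two sections of one document name different tests for the main hypothesis, and the sample size rests on only one of them. This is more than a detail left to a fuller plan, because the article states its analysis in both places and the statements disagree.

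The wording of the analysis section also points to a model that does not suit the data. In the same paragraph, a one-way MANOVA means a model with one between-patient factor (group, at baseline). Read the same way, a two-way MANOVA puts group and time on an equal footing. An analyst who follows that text would enter time as a fixed factor in a 12-cell model with 72 x 3 = 216 rows, so that three scores from one patient count as three patients.

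The group main effect would then be tested against an error term that is too small, and time and group-by-time against one that is too large. A difference between arms in change from baseline appears in group-by-time, so a real treatment effect would be the hardest thing to detect, while a chance imbalance between arms could pass as a significant group effect.

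**Working it through.** **Inputs from the article.** Four groups, equal allocation, 18 per group, 72 in all; three measurements per patient; effect size f = 0.25, alpha 0.05, power 0.80, required N 64; dropout 10%.

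**Assumptions not in the article.** Within-patient correlation rho = 0.3, 0.5 or 0.7; compound symmetry; SD 1 at every visit; for power, one arm gains 0.4 SD at week 4 and 0.8 SD at week 6 and the others do not change.

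**1. The plan's own figure.** For a repeated-measures ANOVA with m = 3 times, the noncentrality is f² x N x m / (1 + (m - 1) x rho) for the group test and f² x N x m x eps / (1 - rho) for the interaction (eps is the sphericity correction). N is rounded up to a multiple of 4. N = 64 is reproduced by:
- the group test with rho = 0: 0.0625 x 64 x 3 = 12.0, power 0.813;
- the interaction with rho = 0.2, eps = 1: 12.0 / 0.8 = 15.0, power 0.820;
- the interaction with rho = 0.5, eps = 0.5: 12.0 x 0.5 / 0.5 = 12.0, power 0.813.

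The article does not say which applies. Dropout gives 64 / 0.9 = 71.1, and 72 covers it. The sample size is thus compatible with the repeated-measures ANOVA that its section names.

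**2. Degrees of freedom.** The literal two-way model has 216 - 12 = 204 error df. The repeated-measures analysis has 72 - 4 = 68 between patients and 68 x 2 = 136 within.

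**3. Why the error rates shift.** Under no effect, the expected mean square is 1 + 2 x rho for group and 1 - rho for group-by-time. The pooled within-cell error of the literal model has expectation 1. So the group F ratio is too large by a factor of 1.6 / 2.0 / 2.4, and the interaction F ratio is shrunk to 0.7 / 0.5 / 0.3 of its proper size. The 5% critical values are 2.65 (3 and 204 df) and 2.14 (6 and 204 df). Dividing by these factors gives effective thresholds of 1.66 / 1.32 / 1.10 for group and 3.06 / 4.29 / 7.14 for interaction. The tail areas are about 18 / 27 / 35% and about 0.7 / 0.04 / 0%.

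**4. Simulation under no effect, one outcome (nominal 5%).**

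| rho | Group, literal | Time, literal | Group-by-time, literal | All three tests, repeated measures |
|---|---|---|---|---|
| 0.3 | 17.6% | 1.5% | 0.8% | about 5% |
| 0.5 | 26.9% | 0.2% | 0.05% | about 5% |
| 0.7 | 35.2% | 0.01% | about 0% | about 5% |

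This agrees with step 3. With four outcomes analysed jointly (the number of primary outcomes, with an assumed correlation of 0.3 between them), the literal group test rejects 34 / 55 / 72%, and the interaction test at most 0.05%.

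**5. Power for group-by-time.** Under the assumed gain, the interaction deviations over the three visits are (-0.3, 0, 0.3) in the treated arm and (0.1, 0, -0.1) in each of the other three. Their squares sum to 0.18 + 3 x 0.02 = 0.24, and 18 x 0.24 = 4.32. The repeated-measures noncentrality is 4.32 / (1 - rho) = 6.17 / 8.64 / 14.4, which gives power of about 40 / 55 / 80% on 6 and 136 df. Simulation gives 39 / 53 / 80%. The literal model gives about 16 / 8 / 2%.

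**The case against.** The strongest reply is that independence is inferred and not stated. The analysis section gives no row structure and no error term. MANOVA is also a recognised way to analyse repeated measures: a doubly multivariate model takes the visits of one patient together and handles their correlation. The sample size section, the mention of effects in an ANOVA, and the planned follow-up of time within group and group within time all fit a repeated-measures analysis that was loosely named. This stands. A reader might infer that the article treats repeated scores as independent, or that only a repeated-measures ANOVA suits the data. It supports neither. The error rates are conditional on the literal reading.

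A reader might also infer that every planned test is invalid. That goes too far. With equal variances, between-group comparisons at week 6 keep about 5% type I error even in the literal model, because they compare different patients at one visit. The plan makes these comparisons only after a significant effect, however, so a nearly closed interaction test still stands in their way.

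A third tempting claim is that, in addition, every patient with a missed visit would be dropped. This does not fit the reading behind the error rates: in a 216-row model a missed visit removes one row. Whole patients are lost in a wide-format repeated-measures analysis, where the error-rate problem does not arise. The two harms cannot be added together.

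None of this removes the disagreement between the two sections. It leaves a choice between models with very different error rates open to whoever runs the analysis.

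**Conclusion.** The point holds as a conflict between two sections, with a conditional statistical consequence. The conflict is certain. The consequence follows only if time is entered as an ordinary factor, which is the plain reading of the analysis section but not the only possible one.

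On that reading, for a single outcome, the group main-effect test has three to seven times its nominal error (18 / 27 / 35% against 5%), and the group-by-time test loses most of its power. The size depends on assumed correlations, compound symmetry and an assumed gain, none of which the article gives. The direction is the same for any positive within-patient correlation. If a doubly multivariate repeated-measures MANOVA was intended, these figures fall away and the text needs only to say so and to agree with the sample size section.

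**What to change.** In the Statistical analysis section, replace the two-way MANOVA with one model per outcome that treats time as a within-patient factor. Either of two will do:
- the repeated-measures ANOVA already named in the Sample size calculation section; or
- preferably, a linear mixed model with patient as the repeated unit and terms for group, visit and group-by-visit, which also keeps patients who miss a visit.

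Name group-by-time, with the between-group contrasts at week 6, as the test of interest, and make the two sections agree.

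The cost is wording. No new data are needed, and the planned SPSS software fits both models. If the mixed model is chosen, add a short note that the figure of 64 was derived under repeated-measures ANOVA.

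### Baseline is analysed as an outcome time and not as a covariate, which dilutes the group effect and costs power

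*Protocol article*

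**What the plan says.** All outcomes are measured "at baseline, at 4 weeks of intervention, and at 6 weeks of intervention" (Data collection). The Statistical analysis section crosses the four arms with "time (e.g., pre-intervention, during intervention, post-intervention", "in order to examine group effect and time effect and The interaction effect of time and group". Effects that are significant go on to Bonferroni-corrected pairwise comparisons, including arms against each other within each time. No covariate is mentioned, and none of the three effects is named as the one that decides.

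Baseline data have one other use: "One-way multivariate analysis of variance will be used to compare the baseline age, height, and weight data of participants".

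The Sample size calculation section rests on the same layout: "According to the experimental design of 4 (group) * 3 (time) in this study, repeated measures analysis of variance was used". That section speaks of repeated measures ANOVA and the Statistical analysis section of two-way multivariate ANOVA. Baseline is a level of time under either name.

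**The concern.** Baseline is measured before any treatment, so in a randomised trial the expected difference between arms at that visit is zero. Averaging it with weeks 4 and 6 pulls the group effect towards zero. Because the plan does not single out the interaction, a diluted group effect can be the result that opens pairwise testing, or the one that is reported as the treatment effect.

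The comparisons of arms within each time have a separate weakness. They use that visit's scores alone, although each patient's baseline on the same outcome is available and predicts the later score. With about 16 to 18 patients per arm, precision is scarce.

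**Working it through.** **Inputs from the article.** Four arms, three times; "Under the effect size of 0.25, α of 0.05, and power of 0.8, the sample size requirement was 64 people"; 10% dropout, 72 randomised, 18 per arm. Evaluable per arm: 64/4 = 16. Four arms give 4 × 3/2 = 6 pairs, so the Bonferroni level is 0.05/6 = 0.0083 if all pairs are compared.

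**Assumptions.** The article gives no within-patient correlation; I use rho = 0.3 / 0.5 / 0.7. The effect d = 0.8 SD, equal at weeks 4 and 6, borrows the article's label for a large effect and is not a planning value. Variances are equal and all pairs of visits share the same rho.

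**Step 1: the plan's own figure.** With the noncentral F for f = 0.25, the 64 reproduces as a between-group effect at rho = 0 (noncentrality f² × N × 3/(1 + 2 rho)), or as the interaction at rho = 0.2 (noncentrality f² × N × 3/(1 − rho)). It also reproduces as the interaction at rho = 0.5 with a sphericity factor of 0.5. The article does not say which effect or correlation was used. If it was the group effect, rho = 0.5 would leave 49% power with 64 patients.

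**Step 2: dilution.** Group effect = (0 + 0.8 + 0.8)/3 = 0.533 SD, two thirds of 0.8. If the effect instead builds as 0, half, full, it is (0 + 0.5 + 1)/3 = half of the week-6 effect.

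**Step 3: variance per patient, V (SD = 1).**
- Three-visit mean: (1 + 2 rho)/3 = 0.533 / 0.667 / 0.800
- Raw week 6: 1
- Week-6 change: 2(1 − rho) = 1.4 / 1.0 / 0.6
- Baseline-adjusted week 6: 1 − rho² = 0.91 / 0.75 / 0.51, multiplied by 1 + 1/(2n − 4) = 1 + 1/28 for estimating the slope

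Change against adjustment at a single week, before that slope factor: 1.4/0.91 = 1.54, 1.0/0.75 = 1.33, 0.6/0.51 = 1.18.

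**Step 4: pairwise power.** Noncentral t, noncentrality = effect/√(2V/16), two-sided alpha 0.05/6, 30 degrees of freedom (29 with the covariate). At rho = 0.5, for example, the three-visit mean has 0.533/√(2 × 0.667/16) = 1.85 and adjusted week 6 has 0.8/√(2 × 0.75 × 1.036/16) = 2.57.

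| Comparison of two arms | rho 0.3 | rho 0.5 | rho 0.7 |
|---|---|---|---|
| Three-visit mean | 25% | 19% | 15% |
| Raw week 6 | 31% | 31% | 31% |
| Week-6 change | 20% | 31% | 55% |
| Baseline-adjusted week 6 | 33% | 41% | 61% |

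**Step 5: omnibus tests.** Take N = 64, alpha 0.05 and assumed arm effects 0.8 / 0.5 / 0.3 / 0 SD at both later weeks. Power of the group effect is 38 / 31 / 26%, of the interaction 33 / 46 / 72%, and of a baseline-adjusted comparison of week 6 alone 49 / 58 / 76%. Here the slope costs only the degree of freedom.

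**The case against.** The strongest reply is that the plan also tests the interaction. That test compares arms on change, is not diluted by the baseline visit and is valid under randomisation. This stands. A reader might infer that baseline outcomes are never used, or that the planned tests are biased; the article supports neither. Setting the three-visit mean against the adjusted analysis also flatters the case. At rho = 0.7, week-6 change reaches 55% against 61% with adjustment, a gap of 6 points. Adjustment is still better at each correlation shown, and the plan does not make the interaction decisive.

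A reader might also think that unadjusted week-6 comparisons carry the whole of any chance baseline imbalance. On average they carry rho times it, which is half at rho = 0.5.

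The gain depends on a correlation that the article does not give. The entry limits (VAS of at least 2, Lysholm below 70) truncate two primary outcomes at baseline and may lower it. At rho = 0.3, adjustment raises week-6 power only from 31% to 33%. At very low rho, the three-visit mean can even beat a single week, because it averages two treated visits: its variance on the scale of the full effect is 0.75(1 + 2 rho), below 1 when rho is under 1/6. The dilution of the estimand remains.

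The baseline test of age, height and weight tells nothing about the baseline outcomes, but no decision hangs on it and it alters no treatment estimate. I do not rest the point on it.

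Finally, an unseen analysis plan might hold more. The article itself, however, makes baseline a level of time, so this is a stated choice and not an omission.

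**Conclusion.** The point holds as a matter of efficiency and of what the group effect estimates. The planned group effect is two thirds of an effect equal at weeks 4 and 6, and less if the effect builds over time. The by-time comparisons forgo the baseline outcome, and the interaction recovers only part of that information. For rho from 0.3 to 0.7 under the stated assumptions, adjusted week-6 power exceeds raw week 6 by 2 to 30 points, week-6 change by 13 to 6 points, and the three-visit mean by 8 to 46 points. The plan is not invalid. Even with adjustment, pairwise power at 0.8 SD stays between 33% and 61%, so this change alone does not make the six comparisons well powered.

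**What to change.** In the Statistical analysis section, take baseline out of the time factor. Model weeks 4 and 6 with group, time, group by time and the baseline value of the same outcome as covariate. State that conclusions rest on the baseline-adjusted week-6 differences between named arm pairs, with 95% confidence intervals and the planned Bonferroni correction, and not on a group effect averaged over three visits.

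In the Sample size calculation section, say that the 4 × 3 ANOVA calculation no longer matches the primary analysis model.

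The cost is one degree of freedom for the covariate and the wording of two sections. Every baseline value is already due to be collected, so no patients, visits or measurements are added.

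### Single-step Bonferroni for the arm comparisons is valid but stricter than 5% familywise control needs; a step-down test would be a cheap improvement

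*Protocol article*

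**What the plan says.** The Study design section sets four parallel arms: the sample was "randomly divided them into 4 groups: TT + KT group, TT + KTp group, KT group, and CON group with a ratio of 1:1". The Sample size calculation section sizes the trial on an omnibus test: "According to the experimental design of 4 (group) * 3 (time) in this study, repeated measures analysis of variance was used". It continues: "Under the effect size of 0.25, α of 0.05, and power of 0.8, the sample size requirement was 64 people". After allowance for dropout, "the final sample size was determined to be 72 people, and each group was about 18 people".

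The Statistical analysis section plans a two-way multivariate analysis of variance "in order to examine group effect and time effect and The interaction effect of time and group". Follow-up testing depends on that result: "Pairwise comparisons of variables with significant effects in ANOVA will be conducted by post hoc analysis and Bonferroni correction". These follow-up tests run in both directions: between visits within an arm, and between arms at a visit. The section does not say which of the three effects must be significant before arm pairs are compared at a visit. It does not give the number of comparisons that Bonferroni divides by, and no power is stated for any arm pair.

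**The concern.** The trial's question is which of the combination, Tan Tui with placebo tape, tape alone or usual activity does better. That is answered by arm pairs, not by an omnibus test. Six pairs under single-step Bonferroni each face 0.0083, whatever the other five show. Once some equalities among the four arms have been rejected, fewer of the rest can still be true, and Bonferroni ignores this. With 18 per arm, power for a single pair is modest, so significance level left unused turns some real differences into non-significant ones.

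**Working it through.** **Inputs.** Four arms (Study design); 18 per arm, f = 0.25, α = 0.05 (Sample size calculation); Bonferroni after a significant effect (Statistical analysis). Assumed, because the article does not state them: two-sided tests, normal data with equal variances, and a family of the six arm pairs for one outcome at one visit. The SD differences are illustrative, since no means or SDs are given.

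**The plan's own figure.** N = 64 reproduces from the noncentral F distribution, but only under a correlation (ρ) and sphericity value (ε) that the article does not state. Examples are the between-group effect with ρ = 0 (power 0.813), the interaction with ρ = 0.2 and ε = 1 (0.820), and the interaction with ρ = 0.5 and ε = 0.5 (0.813). For dropout, 64/0.9 = 71.1 and 64 × 1.1 = 70.4; either leads to 72 = 4 × 18. So the trial is sized for the omnibus test only.

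**Step 1, the family.** 4 × 3/2 = 6 pairs; 0.05/6 = 0.0083.

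**Step 2, how many pairwise nulls can be true.** All four arms equal: 6. Three equal and one apart: 3. Two and two: 2. One equal pair only: 1. All different: 0. Once one pair is rejected, at most 3 of the other nulls can be true. This gives Shaffer's divisors 6, 3, 3, 3, 2, 1, against 6, 5, 4, 3, 2, 1 for Holm and 6 throughout for Bonferroni. The first divisor may drop to 3 only if a separate test has already rejected equality of these same four means.

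**Step 3, one contrast in isolation.** Pooled t test, df = 4 × 17 = 68, noncentrality = d × √(18/2) = 3d.
- d = 0.5: 12.0% power at 0.05/6, 17.7% at 0.05/3
- d = 0.8: 38.2%, 48.2%
- d = 1.0: 61.2%, 70.6%
- d = 1.2: 80.8%, 87.1%

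**Step 4, full procedures.** Simulation with 18 per arm, 40,000 runs per pattern, each behind a 3-df group F test at that visit. Entries are power per true contrast.

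| Arm means (SD units) | Bonferroni | Holm | Shaffer 6,3,3,3,2,1 | Shaffer 3,3,3,3,2,1 |
|---|---|---|---|---|
| 0.8/0/0/0 | 0.38 | 0.41 | 0.44 | 0.46 |
| 1.0/0/0/0 | 0.61 | 0.64 | 0.68 | 0.69 |
| 0.9/0.9/0/0 | 0.50 | 0.54 | 0.57 | 0.59 |
| 1.2/1.2/0.4/0, contrasts of 0.8 | 0.38 | 0.45 | 0.48 | 0.48 |
| 1.2/1.2/0.4/0, contrasts of 1.2 | 0.81 | 0.83 | 0.85 | 0.87 |
| 0.5/0.5/0/0 (f = 0.25) | 0.12 | 0.13 | 0.14 | 0.16 |
| 0.577/0/0/0 (f = 0.25) | 0.17 | 0.18 | 0.20 | 0.22 |

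The f values are the SD of the four means: 0.5/2 = 0.25, and 0.577 × √3/4 = 0.25. With 16 evaluable per arm and means 1.0/0/0/0, the four figures are 0.54, 0.57, 0.61 and 0.63, so the gains are similar.

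**Step 5, familywise error.** Bonferroni behind the F test: about 0.04 with all arms equal, 0.02 with one arm different, 0.02 with two and two. Shaffer 3,3,3,3,2,1 behind the F test: about 0.05, 0.04 and 0.03. No correction after the F test: about 0.12 with one arm different and 0.09 to 0.10 with two and two.

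**Step 6, the plan's actual condition.** Suppose a time effect alone opens the comparisons while all four arms are equal. Shaffer 3,3,3,3,2,1 then has familywise error of about 0.074 to 0.077. Holm and Shaffer 6,3,3,3,2,1 stay at 0.041.

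**The case against.** The strongest reply is that Bonferroni is a valid and familiar choice, and that preferring another procedure is advice on efficiency. That stands: nothing here is wrong, and the point ranks accordingly. It remains worth making because the method is fixed in the text and the change costs one sentence.

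A reader might infer that testing behind a significant ANOVA and then applying Bonferroni corrects twice for one risk. It does not. With four arms, an omnibus F test protects only when all arms are equal, and uncorrected tests after it run at roughly 9 to 12% (step 5). A group F test itself costs at most about 1 point of power per contrast; nearly all the loss comes from the divisor of 6.

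A reader might also infer that a divisor of 6 is never needed once the ANOVA is significant. The plan does not support this, because its condition can be met by a time effect alone, with all six pairwise nulls still true (step 6).

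The larger patterns in the table have f of about 0.43 to 0.52 (1.0/0/0/0: 1.0 × √3/4 = 0.43), nearly twice the planning value or more. That objection stands too, and the gains near f = 0.25 are small. If the interaction is what opens the comparisons (ρ = 0.5 assumed), even the most favourable Shaffer rule gains only 1.4 to 3.1 points there.

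Finally, the protocol lists four primary outcomes and two follow-up visits, with no adjustment stated across them. A less strict rule within each family adds some false positives across the trial. That multiplicity exists equally under the present text, and this change neither causes nor cures it.

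**Conclusion.** Holds as a cheap improvement. Within one outcome and visit, single-step Bonferroni over six arm pairs is more conservative than 5% familywise control requires. For true differences of 0.8 to 1.2 SD, the gain per contrast is about 2 to 7 points with Holm, 4 to 10 with Shaffer 6,3,3,3,2,1, and 6 to 10 with Shaffer 3,3,3,3,2,1 behind a group F test. Near f = 0.25 it is about 1 to 5 points. A gain of 6 to 10 points for every contrast, or one at no cost at all, should not be read into this: those figures need large differences and an added group test, and simultaneous intervals are lost. The conclusion rests on the six-pair family, two-sided tests, normality and equal variances.

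**What to change.** In the Statistical analysis section, before the data are analysed, name the family as the six arm pairs within each outcome and visit. Replace Bonferroni for those comparisons by a step-down test that is valid whichever ANOVA effect is significant: Holm (ordered P values against 0.05/6, 0.05/5, 0.05/4, 0.05/3, 0.05/2, 0.05) or Shaffer (divisors 6, 3, 3, 3, 2, 1), stopping at the first failure.

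Use divisors 3, 3, 3, 3, 2, 1 only if a 3-df group test of the same means at that visit, at 0.05, is written in as the condition for comparing pairs. Do not drop the correction altogether.

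The cost is a sentence or two and a short calculation on P values that SPSS already produces. No extra patients are needed. Step-down decisions have no matching simultaneous confidence intervals. If Bonferroni intervals are still shown, the report should say that a contrast can be significant under the step-down rule while its interval includes zero. Multiplicity across outcomes and visits needs its own decision.
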